##### Engagement

Engagement will be measured via the Twente Engagement with eHealth Technologies Scale (TWEETS) [62], a 9-item self-report scale that can be used to measure expectations of current or past engagement with digital interventions. In this study, the expected and past engagement will be assessed. The questions are answered on a 5-level scoring system in which higher scores indicate higher levels of treatment engagement. The total score is derived by summing the individual scores for each of the 9 items on a scale of 0 to 4; consequently, total scores range from 0 to 40. The TWEETS has shown to be a valid tool that possesses good psychometric qualities to assess engagement with eHealth technologies [63].

##### Short-Form Posttraumatic Stress Disorder Checklist for Diagnostic and Statistical Manual of Mental Disorders, 5th Edition

The short-form version of the posttraumatic stress disorder (PTSD) Checklist for Diagnostic and Statistical Manual of Mental Disorders, 5th Edition (DSM-5), or PCL-5 [64], is a 4-item self-report scale that screens for PTSD symptoms according to the DSM-5. The items are rated on a scale of 0 (not at all) to 4 (extremely). Higher scores indicate a higher likelihood for the screened individuals to fulfill the criteria of PTSD according to the DSM-5. However, the PCL-5 is meant to provide a provisional PTSD diagnosis in circumstances where a structured clinical interview is not feasible. The short-form PCL-5 has been previously validated in the Dutch population and has proven to be a reliable and valid tool [65].

##### Short-Form PCL-5 – COVID-19

Given the unprecedented situation that emerged due to the global COVID-19 pandemic, we decided to include a modified version of the short-form PCL-5 that measures only stressors tied to the COVID-19 pandemic. The short-form PCL-5 – COVID-19 scale that we used for this study is identical to the previously introduced short-form PCL-5; however, we specifically asked participants to indicate on this scale only stressors that are associated with the COVID-19 pandemic.

##### Urgency, Premeditation, Perseverance, Sensation Seeking, Positive Urgency Impulsive Behavior Scale

The reason we decided to include this measurement tool is due to the fact that impulsivity is a significant risk factor for the initiation, continuation, and problematic alcohol consumption [66]. Impulsivity will be assessed via the short-form Urgency, Premeditation, Perseverance, Sensation Seeking, Positive Urgency (UPPS-P) Impulsive Behavior Scale [67]. This short-form version of the UPPS-P is a 20-item self-report scale designed to measure factors that can lead to impulsive behaviors. The questionnaire items are scored on a scale of 1 (strongly disagree) to 4 (strongly agree). The UPPS-P contains five subscales, namely, positive urgency, negative urgency, (lack of) premeditation, (lack of) perseverance, and sensation seeking. The UPPS-P has been tested in healthy, student, and forensic psychiatry settings involving Dutch participants and is considered a reliable and valid tool [68].

#### Sociodemographic Variables

At baseline, sociodemographic variables such as sex, age, level of education, employment, and marital status will be assessed.

### Statistical Analyses

After the data collection period, we will clean our data and assess it for accuracy and completeness. Missing data will be handled using either multiple regression imputation techniques or full information maximum likelihood estimation, depending on the amount of missing data and whether it is missing at random or not. All analyses for the primary and secondary outcomes will use linear mixed modeling regression analyses with the three time points nested within participants. For continuous outcomes, linear models will be used for normally distributed data and negative binomial models, for left-skewed data. For dichotomous outcomes, such as whether or not participants had a binge-drinking episode in the past 30 days, binary logistic regression will be used. All primary analyses will be conducted in line with the intention-to-treat (ITT) principle (ie, including all participants that are randomized). Sensitivity analyses will be conducted in line with the per-protocol principle (ie, intervention completers) and with study completers only. All statistical tests use a significance level α=.05. Time will be used as predictor and baseline measures will be included as covariates if appropriate. All analyses will be conducted using the R Statistical Package. Cohen *d* values will be used as the measure of effect size. Effect sizes of 0.8 are assumed to be large, effect sizes of 0.5 are assumed to be moderate, and effect sizes of 0.2 are assumed to be small [69]. In addition, several intervention effect moderators that might moderate drinking levels based on findings of previous studies will be investigated. In addition, potential moderators such as gender [70], readiness to change [71], engagement [72], and impulsivity [73] will be explored.

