### Inclusion Criteria

Young adults will be eligible for the RCT if they meet the following criteria: (1) aged between 18 and 30 years, (2) willingness to develop healthy lifestyle behaviors and low-risk drinking habits, (3) provision of informed consent digitally, (4) proficiency in reading and writing in Dutch, (5) access to an Android or IOS device with connection to the internet, and (6) possession of an email address. We did not apply a minimum drinking severity inclusion criterion. Our reasoning for not screening drinking severity is based on the fact that the Dutch drinking guidelines recommend an alcohol consumption level of zero or no more than 1 alcoholic drink per day.

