#### Primary Outcomes

##### Alcohol Consumption, Frequency, and Quantity

The primary outcome is the quantity and frequency of alcohol consumption in terms of standard drinks (10 g ethanol per standard drink) per month; this will be assessed through the timeline follow-back (TLFB) method [44], which measures alcohol consumption during the prior 30 days in terms of number of standard drinks. The TLFB is widely used in obtaining data on the frequency of occurrence of drinking behavior, has been evaluated in various clinical and nonclinical populations, and has been shown to have good psychometric characteristics [45,46].

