##### Readiness to Change

The Readiness to Change Questionnaire (RCQ) [47] is a 12-item self-report questionnaire assessing participants’ readiness to change according to the three stages of change: precontemplation, contemplation, and action. The items are rated on a 5-point scale from –2 (totally disagree) to 2 (totally agree). The scores of each stage of change are calculated by adding the individual item scores of the relevant scale. The range of each scale is –8 through 0 to +8. A negative score indicates an overall disagreement with the items measuring the particular stage of change, whereas a positive score represents overall agreement. The RCQ has previously been applied in Dutch clinical settings and has proven to be a reliable and valid tool to measure an individual’s readiness to change [48,49].

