##### Cannabis Use Frequency and Quantity

Cannabis use frequency was assessed using the TLFB method [51]. Furthermore, we asked participants to estimate the quantity of cannabis consumed (in grams) during the previous 30 days. The TLFB method has shown to collect reliable and psychometrically sound information about individuals’ daily cannabis use [52].

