##### Mental Well-being

The Warwick-Edinburgh Mental Wellbeing Scale (WEMWBS) [56] is a 14-item self-report scale that measures positive mental well-being. The items are rated on a scale of 1 (none of the time) to 5 (all of the time). Higher scores indicate higher levels of positive mental well-being among respondents. The WEMWBS has been previously validated in a Dutch setting and has proven to be a reliable and valid tool to measure individuals’ mental well-being [57].

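### The skewness rule points the wrong way: it reserves negative binomial models for left-skewed data and leaves a plausibly right-skewed primary drink count without a clearly assigned model

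*Protocol article*

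**What the plan says.** The Statistical Analyses section makes two statements about model form. The first is general: "All analyses for the primary and secondary outcomes will use linear mixed modeling regression analyses with the three time points nested within participants". The second, given for continuous outcomes, is that "linear models will be used for normally distributed data and negative binomial models, for left-skewed data". Dichotomous outcomes go to logistic regression. No branch is given for right-skewed data, counts are not named as a class, and Cohen d is the only effect measure named.

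The primary outcome comes from the timeline follow-back, "which measures alcohol consumption during the prior 30 days in terms of number of standard drinks". On entry, the Inclusion Criteria section says: "We did not apply a minimum drinking severity inclusion criterion". Two secondary outcomes also bear on the point. For the Readiness to Change Questionnaire (RCQ), "The range of each scale is –8 through 0 to +8". The Warwick-Edinburgh scale (WEMWBS) "is a 14-item self-report scale that measures positive mental well-being", with items scored 1 to 5.

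**The concern.** The negative binomial distribution describes overdispersed counts with a long upper tail. Assigning it to data with a long lower tail reverses its use. Followed as written, the rule has three effects:

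- A right-skewed drink count is neither normally distributed nor left-skewed, so the rule gives it no model. The analyst must fall back on the general linear sentence or guess the intent.
- A readiness-to-change scale that proved left-skewed would go to a likelihood that gives negative scores zero probability.
- Model form depends on the observed shape, with no criterion stated. A linear model estimates a difference in mean drinks, and a log-link negative binomial model estimates a rate ratio. Two analysts following the same text could report different primary effect measures.

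**Working it through.** **1. The plan's own figure.** The Sample Size section gives 253 per arm for g = 0.25, α = .05 and power .80. Sidedness is not stated; two-sided is assumed.

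- Normal approximation: n = 2(1.960 + 0.842)² / 0.25² = 15.70 / 0.0625 ≈ 251.2, rounded up to 252.
- Two-sample t version: 252.13, rounded up to 253.

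The figure reproduces. It uses a standardised mean difference and nothing from the skewness rule, so correcting the rule does not change it.

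**2. Direction of skew.** For a negative binomial variable with size r, mean μ and p = r/(r + μ), skewness = (2 − p) / √(r(1 − p)). Since 0 < p < 1, numerator and denominator are both positive, so skewness is positive for every parameter value. The document gives no SD or dispersion for drinks, so the values below are assumptions:

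| Mean drinks in 30 days | Size r | Skewness |
|---|---|---|
| 5 | 0.3 | 3.65 |
| 20 | 1 | 2.00 |
| 40 | 1 | 2.00 |
| 40 | 2 | 1.42 |
| 60 | 50 | 0.30 |

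For example, at μ = 40 and r = 1, p = 1/41 = 0.0244 and skewness = 1.9756 / √0.9756 = 2.00. Across means of 5 to 60 and sizes of 0.3 to 50, skewness runs from about +0.3 to +3.7.

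**3. Likely shape of the primary outcome.** The document does not report it. The count cannot fall below zero, and light drinkers and abstainers may enter. The Introduction reports that 8.9% of young adults drink more than 21 glasses a week (men) or 14 (women). Over 30 days that is 21 × 30/7 = 90 or 14 × 30/7 = 60 drinks. The guideline cited under Inclusion Criteria is at most one drink a day, or 30 in 30 days. A bulk of low values with a long upper tail is therefore plausible, but it remains an inference.

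**4. Scales under the literal rule.** The negative binomial probability of any negative value is 0, so a single negative RCQ score makes the log-likelihood minus infinity. An illustrative left-skewed variable on −8 to +8 (skewness −0.55, 11% of values below zero) gave exactly that. WEMWBS runs from 14 × 1 = 14 to 14 × 5 = 70. A negative binomial can be fitted to such scores, but with the wrong shape if they are left-skewed.

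**5. Cost of a linear analysis.** A t test was run on simulated negative binomial counts: means 20 and 40, sizes 0.3 to 2, 5,000 trials per setting. Arms were 253 (all randomised) or 154 (half of the 308 with T2 data, equal split assumed). Type I error was 4.2% to 5.6%; the Monte Carlo standard error is √(0.05 × 0.95 / 5000) = 0.3 percentage points.

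A second simulation used a mean of 40 drinks, a 20% reduction, baseline adjustment and 168 per arm (half of the 336 with T1 data), with 1,500 replicates. Power was 53.5% for the linear model and 58.2% for the negative binomial; type I error was 5.3% and 5.7%. These powers depend on dispersion and effect assumptions that the document does not supply, so only the small gap between the models is informative.

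**The case against.** The strongest reply is that this is a slip of terminology. Naming a negative binomial model in a trial whose primary outcome is a drink count suggests that the authors meant data piled up on the left. Changing one word would restore the direction. That is probably right about intent, but the word still has to be changed. Changing it alone would leave the conflict with the all-linear sentence and would leave model form to depend on observed skew.

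It can also be said that the general sentence supplies a default and that detailed model selection belongs in an analysis plan not shown here. Both have some force. The general sentence does name a model for the primary outcome, but the next sentence limits linear models to normally distributed data. The defect is a rule that is stated and wrong, rather than detail left out.

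A reader might infer more than the document supports:

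- *That the primary outcome has no valid analysis.* A linear comparison roughly keeps its type I error at these sample sizes. The skewness rule assigns no model, but a valid analysis is available.
- *That several scales receive an impossible model.* This is strictly true only of the RCQ scales, and only if they prove left-skewed. WEMWBS would be misfitted.
- *That cannabis grams are sent to a count model.* Grams are plausibly right-skewed, so the literal rule does not send them there. Claiming otherwise needs a different reading of the rule from the one that leaves the drink count unassigned.
- *That the trial is wrongly sized.* The sample size does not use the rule.

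**Conclusion.** The point stands as a wrong and internally conflicting rule in the primary analysis text. The direction error is certain, because negative binomial skewness is positive for all parameter values. That the drink count lacks an assigned non-normal model follows from a literal reading together with right skew, which is plausible but undocumented. The practical damage is modest: sample size is unchanged, type I error stays near 5% under a linear analysis, and the power difference is about 5 percentage points under assumed inputs (58.2% − 53.5% = 4.7). What the correction mainly buys is a coherent primary model, and an effect measure settled before comparative results are seen. Nothing in the document shows that a model has been chosen after looking at results.

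**What to change.** Replace left-skewed data with right-skewed count outcomes, reconcile the sentence giving linear mixed models to all outcomes, and assign models by outcome type before comparative data are seen:

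- **30-day standard drinks:** negative binomial mixed model with log link and participant random intercept, reported as a rate ratio with a model-based mean difference in drinks.
- **Questionnaire scale scores, including RCQ and WEMWBS:** linear mixed models.
- **Drinking days and binge days:** these cannot exceed 30, whereas a negative binomial is unbounded. Use a model suited to that bound, or a negative binomial only if values stay far from 30.

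Cannabis grams are not a count and would fall outside the amended negative binomial branch.

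The cost is one paragraph of text, and the primary outcome would carry an effect measure other than Cohen d. No change to sample size or data collection is needed.

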**Methods:**

This two-arm, parallel-group randomized controlled trial will investigate whether a 6-week self-guided mobile intervention (Boozebuster) targeting drinking behavior is more effective than a minimal intervention consisting of an educational website on alcohol use and its consequences for young adults. We will recruit 506 young adults (aged 18-30 years) from the Netherlands via an open recruitment strategy by using an open access website. All outcomes will be self-assessed through questionnaires. The primary outcome is the quantity and frequency of alcohol consumption in standard drinks (10 g ethanol per standard drink) per month (timeline follow-back [TLFB]). Secondary outcomes include binge-drinking sessions per month, alcohol-related problem severity (Rutgers Alcohol Problem Index), cannabis use frequency and quantity in grams (TLFB), depressive symptoms (Center for Epidemiological Studies Depression Scale), perceived stress (Perceived Stress Scale), engagement (Twente Engagement with eHealth Technologies Scale), readiness to change (Readiness to Change Questionnaire), mental well-being (Warwick-Edinburgh Mental Wellbeing Scale), trauma and COVID-19–related trauma (Short-Form Posttraumatic Stress Disorder Checklist for Diagnostic and Statistical Manual of Mental Disorders, 5th Edition), impulsivity (Urgency, Premeditation, Perseverance, Sensation Seeking, Positive Urgency Impulsive Behavior Scale), study or work performance (Individual Work Performance Questionnaire), and treatment adherence. Baseline (T0), 6-week postbaseline (T1), and 3-month postbaseline (T2) assessments will be conducted and analyzed on the basis of the intention-to-treat principle using multilevel mixed modeling analyses.

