### Randomization

First, participants will be screened, asked to fill out the baseline assessment (T0), and then randomized into either the mobile intervention or the educational website group. The allocation sequence will be automatically generated via the computerized Castor EDC system by using a 1:1 allocation ratio with random block sizes of 4 and 6, which also ensures allocation sequence concealment. Participants will be informed about the outcome of the randomization via email by a member of our research team. Initial stratification will be into two groups according to gender (ie, male and female). Within these two groups, participants will be further stratified into two groups categorized by adherence or nonadherence to the Dutch drinking guidelines. Nonadherence will be defined as the consumption of more than 7 drinks per week or at least one binge-drinking session (≥5 drinks for male participants and ≥4 drinks for female participants) in the past 30 days. This will create four strata. Because of the nature of our study design, blinding of group allocation for participants is not possible. Figure 1 provides an overview of the trial flow.

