### Sample Size

Previous meta-analyses assessing drinking reduction in young adults compared to assessment only, attention-matched, or active controls [17,18] found small effect sizes of about g=0.25. Although we expect the Boozebuster intervention to outperform previous interventions in reducing the quantity and frequency of alcohol consumption in comparison to the control condition at the posttest assessments, we decided to base our sample size calculation on this conservative effect estimate. These estimations would result with α=.05 and 1–β=.80 in a sample size of 253 per study arm (ie, N=506).

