##### Binge Drinking

Participants will be asked to indicate the number of binge-drinking days defined as 4 (for females) or 5 (for males) standard drinks on one drinking occasion over the past 30 days.

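### Binge drinking is declared and collected as a count, but the only analysis named for it is any versus none; the count should be named as the secondary outcome and given its own model

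*Protocol article*

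**What the plan says.** Three places give binge drinking as a count or frequency. The Abstract (Methods) states: "Secondary outcomes include binge-drinking sessions per month". Table 1 lists it as a frequency at T0, T1 and T2. The Binge Drinking paragraph says that participants report "the number of binge-drinking days defined as 4 (for females) or 5 (for males) standard drinks on one drinking occasion", over the past 30 days.

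Statistical Analyses mentions binge drinking once: "For dichotomous outcomes, such as whether or not participants had a binge-drinking episode in the past 30 days, binary logistic regression will be used". No paragraph under Outcome Measures declares a yes/no binge outcome.

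Two other statements in Statistical Analyses bear on the point. The first puts every primary and secondary outcome in a mixed model, with the three assessments grouped by participant. The second provides negative binomial models for skewed data (the text says left-skewed, whereas a day count with many values near zero is right-skewed).

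The stratification rule under Randomization uses "at least one binge-drinking session (≥5 drinks for male participants and ≥4 drinks for female participants". It has explicit inequality signs, which the outcome paragraph lacks.

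**The concern.** The outcome sections and the analysis section describe different variables. A reader cannot tell whether the secondary outcome is the number of binge days, any binge at all, or both. The only version with a model named for it is not the one declared. That leaves a choice of version open until after the data have been seen.

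The two versions also carry different information. The app aims at low-risk drinking habits, so a plausible benefit is fewer binge days among people who still binge sometimes. A fall from, say, 6 to 4 days in the month changes the count and leaves the yes/no variable unchanged. If any versus none became the main analysis, the trial could miss an effect that its own data contain.

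**Working it through.** **Inputs from the article.** Two-sided α = 0.05 (the article does not state the sidedness; two-sided reproduces its N), power 0.80, g = 0.25 and 253 per arm (Sample Size); 1:1 allocation (Randomization); 308 completers at T2 (Results).

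**Inputs assumed.** The article gives no mean, dispersion or prevalence of binge days for this sample. I take a control mean μ of 1 to 6 days per month and a negative binomial dispersion k of 0.5 to 2, with variance μ + μ²/k.

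**Step 1: reproduce the plan's figure.** n = 2(1.960 + 0.842)²/0.25² = 251.2, so 252 per arm by the normal approximation. The t-test gives 252.13, so 253. The stated 253 reproduces. It is for alcohol consumption, not binge drinking.

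**Step 2: fix the count analysis at 80% power.** For a Wald test on the log rate ratio RR,

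SE² = [(1/μ + 1/k) + (1/(μ·RR) + 1/k)]/n, and power = Φ(−ln RR/SE − 1.96).

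For each μ and k, choose the RR that gives 80% at n = 253.

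**Step 3: power of any versus none for the same effect.** The share with at least one binge day is p0 = 1 − (k/(k+μ))^k in controls, and p1 is the same with μ·RR. Power comes from the two-proportion test with pooled variance under the null.

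*Worked case, μ = 2, k = 1.* RR = 0.730. SE² = (1.500 + 1.685)/253 = 0.0126, so SE = 0.112. Then 0.314/0.112 − 1.96 = 0.84, which is 80% power. p0 = 0.667 and p1 = 0.594, a difference of 0.073. The standard errors are 0.0429 (null) and 0.0428 (alternative). Power = Φ((0.073 − 1.96 × 0.0429)/0.0428) = Φ(−0.26) = 40%.

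| Mean binge days per month | Count | Any versus none (k 0.5–2) |
|---|---|---|
| 1 | 80% | 51–57% |
| 2 | 80% | 39–40% |
| 3 | 80% | 29–33% |
| 4 | 80% | 23–29% |
| 6 | 80% | 16–24% |

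With T2 completers only (308/2 = 154 per arm, assuming equal loss), the same effects give 59% for the count and 11–38% for any versus none. The planned intention-to-treat analysis also uses T1 data and a missing-data method, so this is a pessimistic view.

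**Step 4: a different model.** Cut a normal variable with d = 0.25 at a control prevalence of 50%, 80% or 90%. Power falls from 80% to 61%, 53% and 41%.

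**Step 5: low prevalence.** The Introduction cites binge drinking in 11.4–19.4% of young adults. Set p0 and solve for μ = k[(1 − p0)^(−1/k) − 1], then repeat Steps 2 and 3 (intermediate values for k = 1):

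| p0 | μ | RR | p1 | Any versus none, k = 1 | k 0.5–2 |
|---|---|---|---|---|---|
| 11.4% | 0.129 | 0.380 | 0.047 | 80% | 78–81% |
| 19.4% | 0.241 | 0.515 | 0.110 | 75% | 71–77% |
| 30% | 0.429 | 0.604 | 0.206 | 69% | 62–72% |
| 50% | 1.000 | 0.690 | 0.408 | 55% | 44–61% |

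At about 11% prevalence most bingers have a single binge day, so the cut costs almost nothing. The cost grows as bingeing becomes more common.

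**The case against.** The strongest reply is that the yes/no sentence offers binge drinking only as an example of a dichotomous outcome. It does not say that the count is replaced. The count stays the declared outcome in three places, and the same section provides a negative binomial model that could take it. In a condensed article, assigning a model to each outcome is commonly left to a fuller plan. This stands in part: the text does not show that the count was abandoned, and a reader who infers that goes too far. But the article does not simply stay silent. It names an analysis for binge drinking, and the variable analysed is not the one declared.

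A reader might also infer that the logistic model ignores the repeated assessments and so inflates type I error. The documents do not support this. The section first places all primary and secondary outcomes in mixed models, then picks the model family by outcome type. None of the three family names (linear, negative binomial, logistic) repeats the word mixed, so the nesting carries over to all of them or to none. At most the wording is loose, because a linear mixed model is not a logistic one.

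A reader might take the outcome definition literally and conclude that a day with six drinks does not count. That is implausible beside the explicit inequalities under Randomization. It is a slip of wording.

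Finally, the size of the loss depends on a binge-day distribution that the article does not give. The cited 11.4–19.4% would make it small, and no minimum drinking level is required at entry. That is a fair limit. Those figures describe young adults in general, though, and this sample is recruited for willingness to adopt low-risk drinking. Its binge prevalence is unknown.

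**Conclusion.** The mismatch is real and can be checked by reading the sections side by side: the secondary outcome is a count, and the only analysis named for it is any versus none. The count has no named model, and two versions remain open.

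Any versus none has clearly lower power in every scenario with a mean of 1 or more binge days and in every latent-normal cut. Against 80% for the count it ranges from 16% to 61%. It is near 80% only if about one participant in ten binges. It would be too strong to say that most of the power is lost. Power falls to half or less at a mean of about 2 days or more, but not at a mean of 1 or under the latent-normal cut. All these figures rest on assumed distributions.

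The point concerns one secondary outcome. The primary outcome and the sample size of 506 are untouched.

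**What to change.** 1. State that the secondary outcome is the number of binge-drinking days in the past 30 days, and analyse it with a negative binomial mixed model with assessments nested in participants. The section already allows negative binomial models for skewed data; name this count there.
2. If any versus none is kept, call it supportive and write the model as mixed-effects logistic regression (or GEE), in line with the section's opening rule on nesting.
3. In the Binge Drinking paragraph, write ≥4 (female) and ≥5 (male) standard drinks, to match the stratification rule under Randomization.

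The cost is a few words and one model specification. The count is already collected at all three assessments, so no new data are needed. The choice should be recorded before outcomes are compared by arm.

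### Adjustment for baseline drinking is optional in a model that already treats baseline as a response; fixing one model in advance would recover precision at no cost

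*Protocol article*

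**What the plan says.** The Statistical Analyses section of the protocol article says that all primary and secondary outcomes will be analysed by "linear mixed modeling regression analyses with the three time points nested within participants". The abstract identifies the three: "Baseline (T0), 6-week postbaseline (T1), and 3-month postbaseline (T2) assessments will be conducted and analyzed". Table 1 confirms that drinking by timeline follow-back is measured at each of them, so baseline drinking is one of the responses. The same section continues: "Time will be used as predictor and baseline measures will be included as covariates if appropriate".

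The section does not say what makes a baseline covariate appropriate. It names time as a predictor, but no arm-by-time term and no constraint that the arms share a baseline mean. Under Randomization, allocation is stratified by whether baseline drinking meets the Dutch guideline.

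**The concern.** In a randomised trial the arms have the same expected drinking at baseline. A good analysis uses that fact, either by conditioning on the T0 value or by modelling T0 with a common mean. The article commits to neither. Three analyses fit its wording:

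- T0 as a response only, with a free mean in each arm. The arm-by-time contrast is then a change-score comparison. It is unbiased but less precise than it could be.
- T0 as both response and covariate. With an arm-by-time contrast, the added covariate gains nothing.
- One arm effect pooled over all three visits. This averages in a visit at which the expected difference is zero.

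At stake are the precision of the primary comparison in a trial that expects heavy dropout and, on the last reading, the size of the reported Cohen d.

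**Working it through.** **Inputs.** Effect: the Sample Size section says that earlier meta-analyses "found small effect sizes of about g=0.25". Allocation is 1:1 (Randomization). Counts are 506 at T0, 336 at T1 and 308 at T2 (Results, as of May 2021), taken as 253, 168 and 154 per arm. Assumptions not in the article: SD 1, equal correlation rho between any two visits with rho from 0.3 to 0.7, monotone dropout that is balanced across arms and ignorable, no effect at T0 and the same effect d at T1 and T2.

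**The plan's own figure.** The article states: "These estimations would result with α=.05 and 1–β=.80 in a sample size of 253 per study arm (ie, N=506". Two-sided, n = 2(1.96 + 0.842)² / 0.25² = 251.2, so 252 per arm. The t-test version gives 252.1, rounded up to 253. The stated size reproduces, as one post-baseline comparison without baseline adjustment or dropout. It is not in dispute.

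**Arm-by-time contrast, complete data, 253 per arm.** With free baseline means, the variance per participant is 2(1 − rho). With baseline adjustment it is 1 − rho². The ratio is 2/(1 + rho).

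| rho | variance ratio | power, free means | power, adjusted |
|---|---|---|---|
| 0.3 | 1.54 | 66% | 84% |
| 0.5 | 1.33 | 80% | 90% |
| 0.7 | 1.18 | 95% | 98% |

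**The same contrast at T2 with the reported retention.** Generalised least squares on 253/168/154 per arm, keeping the baseline values of those who drop out; power = Φ(0.25/SE − 1.96).

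| rho | SE, free means | SE, equal means | variance ratio | power, free | power, equal |
|---|---|---|---|---|---|
| 0.3 | 0.125 | 0.108 | 1.33 | 52% | 63% |
| 0.5 | 0.108 | 0.098 | 1.20 | 64% | 72% |
| 0.7 | 0.085 | 0.081 | 1.11 | 84% | 87% |

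Using T1 and T2 as responses with T0 as a covariate gives the same SEs as the equal-means column, so either remedy recovers the loss.

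**T0 as response and covariate.** In 100 simulated trials (253 per arm, complete data, rho 0.6), the arm-by-time contrast at T1 averaged 0.254 with SE 0.080, whether or not T0 was added as a covariate. The addition is harmless but buys nothing.

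**One arm effect pooled over T0 to T2.** With complete data the coefficient is (0 + 0.25 + 0.25)/3 = 0.167, two thirds of the truth at any rho. At the reported retention the factor is 0.51, 0.49 and 0.46 for rho 0.3, 0.5 and 0.7, so 0.25 becomes about 0.13, 0.12 and 0.12. In the same simulation, adding T0 as a covariate to the pooled model left the estimate at 0.170 but gave power of 0.99. In that case the effect size is understated and the test is not harmed.

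**The case against.** The strongest reply is that a journal article need not list its fixed effects. Three nested time points in a randomised trial naturally suggest an arm-by-time contrast, which is unbiased, and an analysis plan that is not shown may settle the rest. Much of this stands, and it rules out several stronger readings.

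- A reader might infer that the treatment effect will be diluted by a third. The article nowhere states a pooled arm effect over T0 to T2, and the figure of one third needs complete data.
- A reader might infer that T0 is planned as both response and covariate. The phrase refers to baseline measures in general, and its condition could equally mean leaving T0 out where it is already a response. Double use is permitted, not planned.
- A reader might infer that the choice will be made after the results are seen. The article gives no timing for this choice; its remark about the end of data collection concerns cleaning and completeness.
- A reader might compare change scores with covariate adjustment in the 154 per arm with T2 data and find 59% against 71% at rho 0.5. That discards the baseline data of dropouts, which a mixed model on all randomised participants keeps. The gap is then 64% against 72%.

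What does not fall away is that the article itself describes the model, gives baseline a fixed role as a response, and makes its other role conditional on an unstated criterion. That is loose wording in what is fixed, not detail left out.

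**Conclusion.** The point holds as a free improvement to the primary analysis, not as a demonstrated error. On the likelier reading, an arm-by-time contrast with free baseline means, there is no bias. The cost at T2 is about 11 percentage points of power at rho 0.3, 8 at rho 0.5 and 3 at rho 0.7. Shrinkage to two thirds, or to about half at the reported retention, arises only if a pooled arm effect is used.

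The sizes rest on an assumed correlation, compound symmetry, a linear model, and counts that may not be final because the study was still in progress. The power figures are lower if dropout is less benign than assumed. The case for adjustment does not depend on the exact rho: the baseline value is already collected, and the trial already stratifies on a category of it.

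**What to change.** For the baseline value of the outcome, delete the *if appropriate* condition and state one model before analysis. Either of these will do, but not both together:

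1. T1 and T2 are the responses, and the T0 value is always a covariate.
2. T0, T1 and T2 are the responses, with baseline means constrained equal across arms.

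In both, include arm-by-time terms and take the treatment effect as the arm contrast at each post-baseline visit. How T0 is transformed in the count models can be left to the trial statistician. The change costs a sentence or two in the analysis section and needs no new data, participants or procedures.
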